#### Data analysis

At T1, we will apply an analysis of covariance of the primary outcome physical function (SPPB scores). This outcome will be used to analyse the difference between the intervention and control group. In case of non-normally distributed data, we will apply a nonparametric covariance model [34]. The secondary outcomes will be evaluated with ANCOVAs, t-tests or distribution independent Mann-Whitney U-Tests. To compare the number of deaths, events leading to discontinuation of the intervention, falls requiring medical attention, and hospital treatments, we will either calculate a χ2-test, Fisher exact test for binary variables or conduct a log-rank-test. Since the number of falls or falling in general has shown to depend on fear of falling and the amount of physical activity, we will perform a mediator analysis to correctly identify the effect of our intervention on falling [35].

Furthermore, we will perform exploratory analyses (multifactorial ANCOVAs and in case of non-normally distributed data adjusted rank transform tests [36]) and dichotomise and evaluate whether the participants in the subgroups setting (community setting, nursing home), sex, rural/urban setting, frailty, and baseline SPPB score show different results in our primary outcome SPPB or in secondary outcomes. We will perform this analysis at T1 and T2.

The evaluation of the intervention will be performed as intention-to-treat (ITT). The ITT analysis will include all randomised participants irrespective of the actual performance of the intervention. In case a participant decides to withdraw consent, we will ask for a final evaluation.

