### Randomisation

Participants will be randomly assigned to either control or experimental group with a 1:1 allocation as per computer-generated randomisation schedule stratified by setting (community [primary care practice, nursing services] or nursing home). Participants will be randomly allocated via a telephone service provided by the Clinical Trial Centre at the University of Marburg (Koordinierungszentrum für klinische Studien [KKS]).

Research assistants will perform the data collection and examinations at baseline (T0) after 6 months of the intervention (T1) and after 12 months of follow up (T2). They will visit each participant either at their home or care home.

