### Statistical analysis

#### Sample size

Sample size calculation was carried out based on expected effects regarding the primary outcome (physical function measured by the Short Physical Performance Battery [13] after 6 months of intervention (T1). A change of 1 point has been shown to be clinically relevant (e.g. predictive of future hospitalisation, health improvement and mortality) [33]. The standard deviation in comparable samples has ranged between 2.6 and 2.8 points [30, 31]. With a conservative approach, we assumed the higher standard deviation (2.8) for our calculation. In an analysis of covariance (including baseline values of the primary outcome), with an R-square of 0.5 for the covariate and a power of 95% (1-β), sample sizes of *n*=103 will be required for each of the two groups. The total sample of 206 participants achieves 95% power to detect differences among the means using an F test with a 5% significance level. The size of the variation in the means is represented by their standard deviation, which is 0.50. The common standard deviation within a group is assumed to be 2.8.

In our pilot study [12] conducted in nursing homes, we experienced a loss of 28% during the 6 months intervention period mainly due to death and hospitalisation. From our experience, the loss of participants recruited in primary care practices will be lower. A British primary care and community based study, which examined a complex nurse-delivered intervention with self-paced exercises and therefore people who are likely to be physically healthier (compared to our participants), experienced a loss of 6% during 3 months [9]. Considering that we are now also recruiting participants in community settings (living at home, primary care) and following a conservative approach, we set the expected loss during the intervention period to 40% (mainly due to death and hospitalisation). Assuming a loss of 40% during the 6 months of intervention we will need a total sample of *n*=345 to achieve adequate power of 95% at our primary endpoint. This will also enable us to achieve enough power for the analyses of secondary endpoints. The study centre Marburg will aim to recruit 230 persons from the community setting and the study centre Witten 115 from nursing homes.

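### The article names baseline SPPB but not the stratification factor, setting, as a covariate in the primary ANCOVA, and it allows secondary outcomes measured at T0 to be tested without their T0 values

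*Protocol article*

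**What the plan says.** The Randomisation section describes 1:1 allocation by a "computer-generated randomisation schedule stratified by setting (community [primary care practice, nursing services] or nursing home".

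The Data analysis section gives the primary analysis as "At T1, we will apply an analysis of covariance of the primary outcome physical function (SPPB scores", with a nonparametric covariance model if the data are not normally distributed. It lists no covariates. The Sample size section names one: "In an analysis of covariance (including baseline values of the primary outcome), with an R-square of 0.5 for the covariate". Setting enters an analysis in one place only, the exploratory multifactorial ANCOVAs, as one of several subgroup factors.

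For the remaining endpoints the plan is: "The secondary outcomes will be evaluated with ANCOVAs, t-tests or distribution independent Mann-Whitney U-Tests". There is no rule for choosing among the three and no statement that the T0 value is used. Table 1 shows EQ-5D-5L, FES-I and the clock-drawing test measured at T0, T1 and T2. The walk record, falls, hospitalisation and death are recorded at T1 and T2 only.

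**The concern.** Stratifying forces the arms to be balanced on setting. If the model then leaves setting out, the variance between settings stays in the error term, and the standard error overstates the real uncertainty.

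The article gives reasons to expect such variance here:

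- Setting coincides with study centre: Marburg is to recruit 230 people from the community and Witten 115 from nursing homes.
- The Sample size section reports a 28% loss in the nursing-home pilot, mainly from death and hospitalisation, and expects a lower loss in primary care.
- The Missing data section gives SPPB = 0 to participants missing because of death or admission.

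A difference between settings in death and admission would therefore pass into the T1 score in a way that baseline SPPB need not absorb.

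For the secondary scales, a t-test or Mann-Whitney test on T1 values discards a baseline measurement that has already been paid for. It also leaves the comparison exposed to chance baseline imbalance.

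**Working it through.** **Inputs from the Sample size section.** Difference 1 point (the SD of the two means is 0.50); within-group SD 2.8; covariate R-square 0.5; 5% F test; 95% power; 206 analysed; 40% loss; 345 randomised.

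**1. The plan's own figure.** Residual SD = 2.8 × √(1 − 0.5) = 1.980. Noncentrality = 206 × 0.5² / 1.980² = 13.14, with 206 − 3 = 203 error degrees of freedom. Power is 95.03% at N = 206 and 94.84% at N = 204, so 103 per arm is the minimum. Then 206 / 0.6 = 343.3, so 344, against 345 stated. The design reproduces. Without the baseline covariate, power at N = 206 would be 72%, which shows how much the plan relies on that one covariate.

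**2. Leaving setting out of the primary model.** Let p be the share of residual variance that setting explains beyond baseline SPPB. The article gives no value, so p is an assumption. Under stratified allocation the true variance of the effect estimate is (1 − p) times what the model without setting reports.

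- Actual alpha = 2 × [1 − Φ(1.96 / √(1 − p))].
- Power with setting in the model: residual SD 1.980 × √(1 − p), one further degree of freedom lost, N = 206.

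| p (assumed) | Actual alpha, setting omitted | Power, setting included | Gain over planned 95.0% |
|---|---|---|---|
| 2% | 4.8% | 95.4% | 0.4 points |
| 5% | 4.4% | 95.9% | 0.9 points |
| 7% | 4.2% | 96.3% | 1.2 points |
| 10% | 3.9% | 96.7% | 1.7 points |

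The last column compares with the planning figure. Against the test that would actually be run without setting, the gain is smaller, because stratification already makes the estimate more stable. In the normal approximation, with z = 1 / (1.980 × √(4/206)) = 3.625, power is Φ((3.625 − 1.96) / √(1 − p)) without setting and Φ(3.625 / √(1 − p) − 1.96) with it. That gives 95.4% v 95.6% at p = 2% and 96.0% v 96.9% at p = 10%.

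**3. How large p might be.** Simulations used 345 participants split 230/115, zero-scoring of 12% in the community and 28% in nursing homes, and a setting difference of 0 or 1 point. The 12% and the setting difference are assumptions; using 28% for nursing homes treats the whole pilot loss as zero-scored.

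- No setting difference: mean standard error 0.327 without and 0.323 with setting. (0.323/0.327)² = 0.976, a 2.4% cut in estimated variance.
- 1-point difference: 0.321 v 0.309, a cut of about 7%. Null rejection was 4.1% v 5.0%, and power 68.7% v 71.3%, a gain of 2.6 points. A second simulation of the same scenario gave 72.5% v 74.2%, a gain of 1.7 points.

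These runs support 2-7% as a plausible range for p.

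**4. Secondary scales.** With T0-T1 correlation r (assumed; the article gives none), adjusting for the T0 value multiplies the residual variance by 1 − r² and the confidence-interval width by √(1 − r²).

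| r (assumed) | Variance multiplier | Width multiplier | Power, if 80% unadjusted |
|---|---|---|---|
| 0.3 | 0.91 | 0.95 | 84% |
| 0.5 | 0.75 | 0.87 | 90% |
| 0.7 | 0.51 | 0.71 | 98% |

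Read the other way, unadjusted intervals are 1/0.866 = 1.15 times as wide at r = 0.5 and 1/0.714 = 1.40 times as wide at r = 0.7.

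**The case against.** **The article may be silent, not wrong.** The Data analysis section lists no covariates, the sample-size wording says that baseline values are included and not that nothing else is, and a full covariate list may sit in an analysis plan that is not shown. This stands against the stronger reading a reader might take, that the primary model adjusts for baseline SPPB and nothing else; the article does not say so. It does not dispose of the point. The article names one covariate, places setting among the exploratory factors, and expressly admits unadjusted tests for outcomes that have a baseline.

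**Setting is not shown to be strongly prognostic.** This also stands. No setting effect on T1 SPPB is given. The SPPB entry floors differ by one point, but baseline SPPB already carries that information. Differential loss combined with zero-scoring is the real argument, and for primary care the article says only that loss will be lower.

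**The low simulated power is not due to omitting setting.** Correct. With N = 345 and residual SD 1.980 the standard error would be 2 × 1.980 / √345 = 0.213, against about 0.32 simulated. Most of that gap comes from the zero scores. Moreover, the simulations fit a linear model to numeric zeros, whereas the Missing data section describes a worst-rank analysis, so they indicate size only.

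**Unadjusted tests have a legitimate place.** They do for outcomes without a T0 value, such as the physical activity record and hospitalisation. A t-test or Mann-Whitney test could also be run on change scores, which would use the T0 value. The article does not say which is meant, so the loss calculated above applies to tests of T1 values alone.

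**Conclusion.** The point holds as a free improvement in precision and specification. It is not an error in the stated figures: the sample size reproduces, and omitting setting neither biases the primary comparison nor inflates its type I error.

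For the primary outcome the effect is small: an actual alpha of about 4.2-4.8% if setting explains 2-7% of residual variance, and roughly 0.4 to 2.6 points of power. The lower figure is measured against the planned 95% and the upper comes from the simulated 1-point setting difference. All of this rests on assumed setting effects.

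For EQ-5D-5L, FES-I and the clock-drawing test the effect can be material: 25-49% of variance at assumed correlations of 0.5-0.7, if the tests use T1 values alone. It does not extend to all secondary outcomes.

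**What to change.** State that the primary model, whether ANCOVA or its rank-based version, includes arm, baseline SPPB and setting.

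State that EQ-5D-5L, FES-I and the clock-drawing test are analysed by ANCOVA, or rank ANCOVA where the distribution requires it, on their own T0 value and setting, in place of unadjusted t-tests or Mann-Whitney tests.

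For outcomes without a T0 value (physical activity record, falls, hospitalisation, death), adjust for or stratify by setting only.

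The cost is wording, to be settled before the allocation code is opened to the statistician. Every variable needed is already collected, and the primary model loses one degree of freedom.

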### Aims

Our research questions are:
Compared to controls, does volunteer-supported walking improve physical function and quality of life as well as lower fear of falling? Furthermore, improves supported walking the cognitive executive function and the general physical activity? [Effectiveness]Compared to controls, does volunteer-support walking increase the rate of falls needing medical attention, rate of admissions to hospital, duration of hospitalisations and mortality? [Safety]Compared to controls, does supported walking have an impact on the frequency and duration of hospitalisations and/or mortality? [effectiveness, safety]

Finally, we explore whether the intervention can be successfully implemented into existing community services.

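### The safety question asks about rates of treated falls and hospital admissions, but the named tests use at most one event per person and give no rate ratio

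*Protocol article*

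**What the plan says.** The safety question in Aims is whether walking will "increase the rate of falls needing medical attention, rate of admissions to hospital, duration of hospitalisations and mortality". The next question there asks whether it will "have an impact on the frequency and duration of hospitalisations and/or mortality". Both concern events that one person can have several times.

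The Data analysis section gives these events a sentence of their own. It begins "To compare the number of deaths, events leading to discontinuation of the intervention, falls requiring medical attention, and hospital treatments" and continues "we will either calculate a χ2-test, Fisher exact test for binary variables or conduct a log-rank-test". It does not say which test goes with which event.

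Two neighbouring sentences could bear on the point. The one before reads "The secondary outcomes will be evaluated with ANCOVAs, t-tests or distribution independent Mann-Whitney U-Tests". The one after says of falls that "we will perform a mediator analysis to correctly identify the effect of our intervention on falling".

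On follow-up, the Sample size section says "we set the expected loss during the intervention period to 40% (mainly due to death and hospitalisation".

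**The concern.** A rate is a number of events divided by time at risk. A chi-square or Fisher test compares the proportion of people with any event, so a person with three treated falls counts the same as a person with one, and a person observed for two months counts the same as one observed for six. A log-rank test handles unequal follow-up but, for falls and admissions, stops at the first event. Neither route produces the quantity that the Aims section asks about.

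This is more than a detail left open. The protocol names methods, and they do not match its own question. The comparison is also one of harm in a frail population. A test that discards repeat events has less chance of showing an excess, and a non-significant result may then be read as reassurance. Repeat falls are to be expected: the Background section reports that more than 10% of people aged 65 to 80 had fallen more than once in a year, and this trial enrols people with reduced physical function.

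**Working it through.** **The plan's own figures.** There is no event rate or power for falls or admissions to reproduce. The SPPB calculation does reproduce: residual SD = 2.8 × √(1 − 0.5) = 1.98; a difference of 1 point at two-sided 5% and 95% power needs 102 per arm by the normal approximation; the F test with 103 per arm has 95.0% power; 206 / 0.6 = 343.3, so 344 against the stated 345. With 1:1 allocation this is about 172 per arm, used below.

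**Inputs.** From the documents: 172 per arm; 28% loss over six months (the nursing-home pilot, Sample size section); 5% significance level. Assumed, because the documents give nothing: treated-fall rates of 0.3 and 0.5 per person per six months (rate ratio 0.5 / 0.3 = 1.67), overdispersion k = 1, and loss times uniform over the six months. For the binary test, a person lost without an event counts as event-free.

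**Step 1: events discarded.** For k = 1 and a mean of μ events over full follow-up, P(any event) = μ / (1 + μ), giving 0.3 / 1.3 = 0.231 and 0.5 / 1.5 = 0.333. For those lost, the average is 1 − ln(1 + μ) / μ, giving 0.125 and 0.189.
- Control: 0.72 × 0.231 + 0.28 × 0.125 = 0.201
- Intervention: 0.72 × 0.333 + 0.28 × 0.189 = 0.293

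Mean follow-up is 0.72 + 0.28 × 0.5 = 0.86 of the period, so expected events for one person from each arm are 0.86 × (0.3 + 0.5) = 0.688. First events are 0.201 + 0.293 = 0.494. The repeat share is 1 − 0.494 / 0.688 ≈ 28% (about 27% in simulation).

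**Step 2: chi-square.** Difference 0.0916; SE = √[(0.201 × 0.799 + 0.293 × 0.707) / 172] = 0.0462; z = 1.98. Power = Φ(1.98 − 1.96) ≈ 51%.

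**Step 3: rate model.** Negative binomial information per person is μt / (1 + kμt), which for k = 1 averages to the same 0.201 and 0.293. Var(log rate ratio) = 1 / (172 × 0.201) + 1 / (172 × 0.293) = 0.0289 + 0.0198 = 0.0487; SE = 0.221; ln 1.667 = 0.511; z = 2.31. Power = Φ(2.31 − 1.96) ≈ 64%.

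**Step 4: simulation, with log-rank added.**

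| Loss, control / intervention | Chi-square | Log-rank | Rate model |
|---|---|---|---|
| 28% / 28%, power | 50% | 51–52% | 64% |
| 20% / 40%, power | 32–33% | 53–54% | 64–66% |
| 20% / 40%, equal rates, rejection | 6.7–9% | 4.4–5% | 4–6% |

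Ranges cover separate runs of 1,500 and 3,000 trials per cell. If the chi-square test uses completers only, the 20% / 40% rows give 44% power and 4.7% rejection.

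**Step 5: sensitivity to the assumptions.** With control rates of 0.5 to 2 events per person-year, overdispersion 0.5 to 1.5, a rate ratio of 1.5 and 40% loss in both arms, chi-square power is 28–50% and rate-model power 34–84%. The gain runs from about 6 points (28% v 34%, rarest events) to about 34 points (50% v 84%). Repeat events are 15–57% of the total across all scenarios in this set. At equal rates with equal 40% loss, both tests stay near 5%. With 30% / 50% loss and lost participants counted as event-free, chi-square rejects in 9–17% of trials and the rate model in 4–6%.

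**The case against.** - **Log-rank is one of the planned tests.** It deals with censoring, so setting chi-square at 32% against a rate model near 65% under unequal loss compares only with the weaker planned option. Log-rank reaches about 53% there. This stands: if log-rank is used, the follow-up problem goes and a loss of about 12 points remains.
- **The 40% is not loss of safety data.** A reader might infer that four in ten participants drop out of the falls and admissions comparison. The documents do not support that. The figure is a deliberately cautious allowance for the six-month SPPB visit. An admission that prevents that visit is itself a counted event, and treated falls are reported by medical staff. Death does still shorten time at risk.
- **Unequal loss is assumed.** The Discussion admits that selective attrition is possible, but nothing predicts a 20-point gap between arms. Nor does the plan say that lost participants count as event-free: the Missing data section refers to worst-rank scoring and multiple imputation, without making clear how either would apply to events. So a reader should not infer that the safety test is invalid as planned.
- **Other sentences might cover counts.** A t-test or Mann-Whitney test could be applied to counts, but the next sentence gives these events their own tests, and neither uses time at risk. The mediator analysis concerns pathways through fear of falling and activity, and names no count model. This does not remove the point.
- **Any event or first event is a legitimate safety summary, and an analysis plan may add more.** True as a supporting summary. It does not answer a question worded as a rate.
- **Discontinuation events.** A reader might infer that comparing these between arms is meaningless, since controls do not walk. That goes too far, because controls have an assigned lecture programme. What counts as discontinuation for them should simply be stated.

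**Conclusion.** The point holds as a mismatch between question and method. Even with complete follow-up, the named tests discard repeat falls and admissions and return no rate ratio. Under the stated assumptions with equal 28% loss, this costs about 12 to 14 percentage points of power (50–52% against 64%). The cost is nearer 6 points against chi-square if events are rare, and much larger if they are frequent. Type I error is at risk only for the binary option, and only when loss differs between arms and lost participants are treated as event-free. The rates, overdispersion and pattern of loss are assumptions; the mismatch does not depend on them. It should be corrected, but it does not touch the primary SPPB comparison.

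**What to change.** Analyse treated falls and hospital admissions with negative binomial regression: arm and setting as terms, log time at risk as offset, dispersion estimated from the data. Report the rate ratio with its 95% confidence interval, and for falls draw attention to the upper limit rather than rely on a non-significant test. Analyse death by time to event. Keep the proportion with any event as a supporting summary. State what a discontinuation event means in the control arm (minor).

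The cost is mainly wording. Table 1 already collects dates of treated falls, admission, discharge and death. There is one small burden: the falls forms are described as asking whether a fall occurred, and no date of withdrawal or moving away is listed. Each treated fall, and the date on which observation ends, must be recorded so that counts and time at risk are complete.

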### Outcomes

We expect the intervention to impact upon muscle strength, balance and ability to walk. We therefore chose the Short Physical Performance Battery as the main outcome of the study. SPPB scores have been shown to be associated with disability in mobility and activities of daily living [26–28], future hospitalisation [29], health improvement [30] and mortality [30–32]. For these simple measures of performance, the SPPB shows a good reliability and validity [27].

As secondary outcomes we will evaluate quality of life (EQ-5D-5L), fear of falling (FES-I), physical activity (activity diary), cognitive executive function (clock drawing test), falls requiring medical attention, hospitalisation and death.

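### As written, the subgroup rule sends yes/no outcomes (treated falls, hospitalisation, death) to the adjusted rank transform, which can give false arm-by-subgroup effects far above 5%

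*Protocol article*

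**What the plan says.** The Data analysis section describes the exploratory analyses by one pair of methods: "multifactorial ANCOVAs and in case of non-normally distributed data adjusted rank transform tests [36". They are to show whether the "subgroups setting (community setting, nursing home), sex, rural/urban setting, frailty, and baseline SPPB score" categories "show different results in our primary outcome SPPB or in secondary outcomes", at both T1 and T2.

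The Outcomes section ends its list of secondary outcomes with "falls requiring medical attention, hospitalisation and death".

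Earlier in Data analysis, the counts of deaths, treated falls and hospital treatments are compared between arms: "we will either calculate a χ2-test, Fisher exact test for binary variables or conduct a log-rank-test". That sentence does not mention subgroups, and none of the tests it names examines an arm-by-subgroup difference as stated. The subgroup sentence makes no exception for event outcomes and names no method for binary or time-to-event data.

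**The concern.** A yes/no variable is never normally distributed. If the subgroup rule covers event outcomes, its non-normal branch applies to them, and that branch is the adjusted rank transform.

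The method suits outcomes with many distinct values. A 0/1 outcome has one very large tie at 0. Subtracting arm and subgroup means breaks that tie into a separate value for each arm-by-subgroup cell. Ranking then turns trivial differences between these values into large rank gaps, and the interaction test responds to cell membership rather than to events.

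Treated falls, admissions and mortality are the trial's safety question (Aims). Setting is the stratification factor and the first-named subgroup, and it is unequal by design. The trial could report that supported walking raises or lowers such events in nursing homes but not in the community when the test alone produced the difference. The article also plans to pass its results to municipalities and care organisations.

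**Working it through.** **Inputs from the protocol article**
- Setting split (Sample size): "The study centre Marburg will aim to recruit 230 persons from the community setting and the study centre Witten 115 from nursing homes", so 230 + 115 = 345.
- Allocation (Randomisation): "1:1 allocation as per computer-generated randomisation schedule stratified by setting". Cells are therefore about 115 and 115 (community) and 57 and 58 (nursing home).
- Level: "using an F test with a 5% significance level". This is stated for the primary analysis and taken here for the subgroup tests.

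**Assumptions not in the article**
- Event risks: 5 to 30%, equal in the two settings or higher in nursing homes.
- Algorithm: the usual form (subtract both main effects, mid-rank, F test of the interaction on the ranks). The article only cites a source for it.

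**The plan's own figure.** A 1-point difference (SD of means 0.50), SD 2.8 and R-square 0.5 give a residual SD of 2.8 × √0.5 = 1.98. The noncentral F test with 103 per group has power 0.9503, as stated. 206 / 0.6 = 343.3, so 344 against the stated 345. The design inputs reproduce. The article states no error rate for the subgroup tests.

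**Why the test fails: an invented data set with almost no interaction**

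Events: community control 11/115, community walking 12/115, nursing home control 11/57, nursing home walking 12/58. The risk differences are 10.43 − 9.57 = 0.87 points and 20.69 − 19.30 = 1.39 points.

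Marginal means: control 22/172 = 0.1279, walking 24/173 = 0.1387, community 23/230 = 0.10, nursing home 23/115 = 0.20.

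Each 0 becomes minus (arm mean + setting mean):

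| Cell | Number of 0s | Value of a 0 | Rank of each 0 | Rank of each event | Mean rank |
|---|---|---|---|---|---|
| Nursing home, walking | 46 | −0.3387 | 23.5 | 305.5 | 81.8 |
| Nursing home, control | 46 | −0.3279 | 69.5 | 317 | 117.3 |
| Community, walking | 103 | −0.2387 | 144 | 328.5 | 163.3 |
| Community, control | 104 | −0.2279 | 247.5 | 340 | 256.3 |

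Within each setting the two blocks of 0s differ by only 0.011. Their rank gap is set by block size: (103 + 104)/2 = 103.5 in the community and (46 + 46)/2 = 46 in nursing homes. The arm difference in mean rank is 93.1 against 35.4, a contrast of 57.7.

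The within-cell mean square of the ranks is 5,137 on 341 df, and the sum of 1/n over cells is 0.0522. So F = 57.7² / (5,137 × 0.0522) = 12.4, p = 0.0005. The same F test on the raw 0/1 data gives p = 0.95.

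**False-positive rate over repeated trials.** Simulation with cells 115/115/57/58, no arm effect in either setting, nominal 5%, 1,000 trials per row (Monte Carlo error at most about 1.6 points):

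| Event risk, community / nursing home | Rank transform | F test on raw 0/1 |
|---|---|---|
| 5% / 5% | 57% | 4% |
| 10% / 10% | 51% | 5% |
| 20% / 20% | 33% | 4% |
| 30% / 30% | 24% | 5% |
| 5% / 10% | 82% | 8% |
| 10% / 20% | 90% | 7% |
| 20% / 30% | 65% | 6% |
| 10% / 30% | 95% | 10% |
| 5% / 20% | 99% | 10% |

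**Sensitivity**
- Aligning on marginal means or by a least-squares fit gives practically the same results. Unweighted cell means give similar or somewhat higher rates.
- A baseline covariate in the F test alone changes nothing. Removing it before ranking as well lowers the rate to 12 to 68%.
- With 206 analysed, the rate is about 13 to 88% over the same risks.
- Near-even splits give about 6 to 20%, and up to about 38% when risks differ strongly (5% against 20%).
- A logistic likelihood-ratio test of the interaction, simulated in the nine scenarios above, rejects in about 5 to 7%. The highest value is at 5%/5%, where cells are sparse.

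**The case against.** The strongest objection is that the article may not mean to send events to this test. In Data analysis, one sentence gives the secondary outcomes ANCOVA, t-tests or Mann-Whitney tests, and the next treats deaths, falls and hospital treatments separately. The abstract and the Aims also set safety apart from effectiveness. On that reading, secondary outcomes in the subgroup sentence means the score outcomes only. This is a fair alternative, and it stands as a limit: the routing is the literal reading, not the only one. But the Outcomes section includes the events in the term, and under the narrower reading events would have no stated subgroup method. Either way the sentence needs its scope fixed.

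It may also be said that the model for an exploratory subgroup analysis belongs in the analysis plan. That would hold if the article were silent. Instead it names a method whose stated scope includes outcomes it does not suit.

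The size depends on an assumed algorithm and assumed risks, and that stands too. So does the exploratory label, which lowers the weight of any subgroup result without making the test valid.

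A reader might infer more than the documents support:
- That every subgroup factor is affected as badly as setting. Frailty and baseline SPPB are to be dichotomised at cut-points not given, and near-even splits are affected much less.
- That the comparison of arms for safety events is unsound. It has its own suitable tests.
- That ANCOVA, the first-named method, shares the fault. On 0/1 data it is only mildly off.
- That the fault extends to walking time, or that the affected tests can be counted. The article gives no distribution for walking time, and it leaves open whether events are analysed as yes/no, counts or times. The simulation covers yes/no outcomes only.

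**Conclusion.** The point holds in a limited form. Read literally, the article assigns subgroup tests of treated falls, hospitalisation and death to a method that does not hold its level on yes/no data.

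For the arm-by-setting test at N = 345 and 230/115, the false-positive rate is about 24 to 99% instead of 5%. This rests on the align-then-rank algorithm, no arm effect and event risks of 5 to 30%. The high end arises when risk differs between settings. That is plausible here, because the Sample size section expects lower losses in primary care than in the nursing-home pilot, where death and hospitalisation were the main causes. The fault lies in the rank-transform branch.

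The primary SPPB analysis, the sample size and the comparison of arms for safety events are not affected. This should be corrected, but it does not threaten the trial's main conclusion.

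**What to change.** In Data analysis, limit the ANCOVA and adjusted rank transform subgroup tests to SPPB and the other score outcomes. Add that for treated falls, hospitalisation and death the arm-by-subgroup term is tested in a logistic model, or in a Cox or count model where time or number is analysed, and that subgroup effects are reported with confidence intervals. Where events are few in a cell, the intervals should carry the interpretation.

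The cost is one sentence of analysis wording. It needs no new data, participants or staff.
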